#### Measures of primary, secondary, and other outcomes

The following measures have been adapted into Romanian and successfully used in two previous trials testing another version of the app, and they have shown adequate psychometric properties [36].

The level of depressive symptomatology is assessed with the Center for Epidemiologic Studies Depression Scale–Revised (CESD-R) [37, 38]. The CESD-R is a 20-item self-report instrument, which measures symptoms of depression in nine different groups: sadness (dysphoria), loss of interest (anhedonia), appetite, sleep, thinking/concentration, guilt (worthlessness), tiredness (fatigue), movement (agitation), and suicidal ideation. Participants rate each item on a 5-point Likert scale, from 0 (not at all or less than 1 day) to 4 (nearly every day for 2 weeks) to indicate how they felt or behaved during the last week or so. The total CESD-R score is calculated as a sum of responses to all 20 questions. The CESD-R exhibited good psychometric properties, including high internal consistency, strong factor loadings, and theoretically consistent convergent and divergent validity with anxiety, schizotypy, and positive and negative affect [39].

*The Positive and Negative Affect Scale* (PANAS) [40] is a 20-item self-report questionnaire designed to assess mood. It consists of 10 items that address positive affect (PA) and 10 items that address negative affect (NA). Participants rate each item on a 5-point Likert scale, from 1 (very slightly/not at all) to 5 (extremely) to indicate how they felt during the indicated time frame. The PANAS can be used to assess mood on various time scales by altering the instructions. For the purposes of this study we have used a 2-week time frame. The validity and internal consistency of the PANAS are good, with test-retest reliability being the highest for the “general” temporal instruction. The PANAS has been used previously on the Romanian population and was found to have adequate psychometric properties [41, 42].

*Satisfaction with Life* (SWL) [43] is a five-item scale designed to measure global cognitive judgments of one’s life satisfaction. Participants rate each of the five items using a 7-point scale that ranges from 7 (strongly agree) to 1 (strongly disagree). The SWL has been shown to be a valid and reliable measure of life satisfaction which can be used with a wide range of age groups [44, 45].

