**Fig. 5 Fig5:**
[figure not shown]
Schedule of enrolment, interventions, and assessments

The participants in the active intervention and active placebo conditions are assessed at preintervention (time 1 – baseline), at mid-intervention (time 2 – 3 weeks after baseline), at post intervention (time 3 – 6 weeks after baseline), and at 3 months post intervention (time 4). The participants in the delayed-intervention condition are assessed before the waiting period (time 1 – baseline), at mid-waiting period (time 2 – 3 weeks after baseline), and at post waiting period (time 3 – 6 weeks after baseline).

Participants assigned to the active intervention condition will be given access to the online application along with explicit instructions regarding the use of all its sections. Participants will be given 6 weeks to complete the intervention, during which time weekly messages will be sent out to them. Messages include regular assignments designed for a complete and thorough use of the application’s courses and exercises, and encourage the review of materials whenever possible. However, participants are free to use the application at their own pace.

Similarly, the participants in the active placebo condition will be given access to a sham version of the app. During the 6-week intervention period they will be exposed to the same amount of online (i.e., in-app messages) and therapist communication as the active intervention participants.

After each week, participants’ app use is evaluated (see the Application Use Scale described above). Similarly, after each week of using the app, the participants are required to complete the CESD-R to monitor their depressive symptomatology and provide individualized in-app feedback on their emotional state.

The participants in the delayed-intervention condition are placed on a wait-list for 6 weeks, after which time they are given full access to the app.

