#### Sample size

A total of 165 participants with moderate depressive symptomatology was estimated. This is based on previous studies on the efficacy of mobile phone applications for depression, which reported small to moderate between-group effect sizes [19, 24]. An a priori sample size calculation was conducted with G*Power 3.1.9.2 [58, 59] for analysis of variance (ANOVA) (repeated measures, between factors), assuming an alpha level of 0.05, a statistical power of 0.80, and a small to medium effect size (*f* = 0.2). Since the current protocol has a therapist check-in component, a sample size recruitment target of *N* = 220 was set to allow for sample attrition, thus estimating a dropout rate of approximately 30%.

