#### Statistical methods

Post-treatment analyses involve an intent-to-treat (ITT) design with the first available data after the baseline carried forward.

Improvement in the primary outcomes measures scores within and between the groups will be examined using mixed-effects linear regression analyses with a random intercept and slope over time (four assessments: baseline, mid-intervention, post intervention, and follow-up) and fixed effects for intervention assignment. The main analysis will compare groups (active intervention, PI, and WL) in terms of the level of depressive symptoms. When the analysis of secondary/other outcomes is performed, the error probability will be adjusted according to the number of group comparisons performed.

App usage data and user activity will be examined by comparing, for example, the participants’ self-reported activity with their actual app usage as recorded by our software. This will inform us about any obstacles to user adherence to the protocol, as well as specific usage patterns.

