### Monitoring study implementation

Three clinical psychologists, members of the study team, screen for the risk of unintended effects or harm to the participants (i.e., clinically significant increase in depressive symptomatology as measured by the CESD-R). Every participant’s CESD-R score is assessed weekly and interpreted clinically by the clinician assigned to them. If the participant does not complete the CESD-R assessment, the clinician will address this issue during the phone check-in. If necessary, the therapist can recommend the interruption of the participant’s access to the application.

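### The primary model takes four CESD-R assessments although both app arms supply the score weekly, so some participants' last score before dropout goes unused

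*Protocol article*

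**What the plan says.** The CESD-R is the primary outcome instrument (Measures of primary, secondary, and other outcomes). Under Participant timeline, for the app conditions, "after each week of using the app, the participants are required to complete the CESD-R to monitor their depressive symptomatology". The section on monitoring study implementation says that the "CESD-R score is assessed weekly and interpreted clinically by the clinician assigned to them".

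Statistical methods plans "mixed-effects linear regression analyses with a random intercept and slope over time", with time given as "four assessments: baseline, mid-intervention, post intervention, and follow-up". It also describes an "intent-to-treat (ITT) design with the first available data after the baseline carried forward". No section gives the scores at weeks 1, 2, 4 and 5 a role in the efficacy analysis. Their stated uses are monitoring and in-app feedback.

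The wait-list arm is assessed at baseline and then "at mid-waiting period (time 2 – 3 weeks after baseline), and at post waiting period (time 3 – 6 weeks after baseline"). No weekly CESD-R is listed for it. Sample size raises recruitment to 220 for attrition, "thus estimating a dropout rate of approximately 30" per cent.

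**The concern.** A likelihood-based mixed model gives a valid contrast under dropout if, given the scores in the model, leaving does not depend on what was not observed. If a participant's leaving follows how they felt in the last week or two, the score that makes this assumption plausible is the latest weekly one. The model as stated omits it unless it falls at week 3.

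The protocol describes a route by which this could happen. Weekly scores are fed back to participants. A clinician who sees worsening can recommend interrupting access to the app. All assessments after screening are collected inside the app. The main aim is app versus active placebo, and those are the two arms with weekly data. At stake is avoidable bias in that contrast and, to a lesser extent, precision.

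**Working it through.** **Inputs from the protocol:** weekly CESD-R in the app arms; primary model at baseline, week 3, week 6 and follow-up; N = 220 in three arms, so 220/3 ≈ 73 per arm; about 30% dropout.

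**Assumed, because the protocol does not give them:** within-person covariance, dropout pattern, and a true week-6 difference of 0.40 SD.

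**1. The plan's own figure.** For a between-factor repeated-measures ANOVA, λ = N·m·f²/[1+(m−1)ρ]. With three groups, m = 3 and ρ = 0.5 (neither m nor ρ is stated), λ = 165×3×0.04/2 = 9.9 and power is 0.804, so 165 reproduces. The step to 220 equals 165/0.75, a 25% allowance. That is a separate matter and does not affect what follows.

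**2. Who is affected.**

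| Last seen at week | Scores in the four-assessment model | Latest score used? |
|---|---|---|
| 0 | 0 | yes, nothing to add |
| 1 or 2 | 0 | no |
| 3 | 0, 3 | yes |
| 4 or 5 | 0, 3 | no |

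If 30% dropout is spread evenly over last-seen weeks 0 to 5, the affected share is 0.30×4/6 = 0.20, or about 15 of 73 per app arm.

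**3. How well a missing week-6 score is predicted (R²).** Under AR(1), R² = ρ^(2×gap in weeks). Under compound symmetry with k observed scores, R² = kρ²/[1+(k−1)ρ]. Example for last seen at week 5:
- AR(1) with ρ = 0.8: 0.8⁶ = 0.26 from the four-assessment data, 0.8² = 0.64 from weekly data.
- Compound symmetry with ρ = 0.5: 0.5/1.5 = 0.33 (k = 2) against 1.5/3.5 = 0.43 (k = 6).

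Over four covariances (compound symmetry 0.5, random intercept and slope, AR(1) 0.8 and 0.9), the ranges are:
- last seen week 2: 0.07–0.28 against 0.17–0.43;
- last seen week 5: 0.26–0.53 against 0.43–0.81.

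**4. Precision of the week-6 difference (SD units, 73 per arm).** Completers only: √[2/(73×0.7)] = 0.198. No dropout: √(2/73) = 0.166. Likelihood fit to scheduled visits: 0.185–0.192. Likelihood fit to weekly scores: 0.181–0.188. The variance ratio is 1.03–1.04. A separate simulation (500 trials per scenario, adjacent-week correlation 0.68–0.80) put the gain at 2.5–7%.

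**5. Bias.** These are likelihood fits with categorical visit to weeks 0, 3, 6 or to weeks 0–6, without carry-forward and without the follow-up visit. They isolate the choice of visits and do not reproduce the whole planned analysis. The true benefit is 0.40 SD.

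| Dropout follows the score | Scheduled visits | Weekly scores |
|---|---|---|
| alike in both arms | 0.38–0.39 | 0.39–0.41 |
| in placebo only | 0.33 | 0.39–0.40 |
| in active only | 0.44–0.47 | 0.39–0.40 |
| in opposite directions, 31–32% dropout | 0.31–0.32 | 0.41 |
| in opposite directions, dropout from 30% to 42% | 0.23–0.28 | 0.39–0.41 |

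A further one-arm calculation with log-odds of 1 per SD gave a bias of 0.03–0.05 SD with scheduled visits and at most 0.01 SD with weekly scores. In the opposite-direction rows the shortfall runs from (0.40−0.32)/0.40 = 20% upwards.

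**6. Interaction with carry-forward.** Suppose the effect grows linearly to 0.40 SD at week 6, 30% drop out at random, and each dropout has a value to carry.
- Carrying week 3 gives 0.70×0.40 + 0.30×0.20 = 0.34.
- Carrying week 1 gives 0.70×0.40 + 0.30×0.40/6 = 0.30.

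Adding weekly scores while the rule stands could make week 1 the carried value and move the estimate further from 0.40.

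**The case against.** Four assessments can be defended. Trial design calls them the major assessments, the weekly scores are described as monitoring and feedback, and the wait-list arm has no weekly schedule, so the shared visits keep the three arms comparable. That is a fair reason for the choice, but it does not bar use of the same scale in the two arms of main interest. A likelihood model accepts unequal schedules.

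A reader might infer from the opposite-direction rows that the planned contrast will come out a fifth or more too small. The documents do not support that. The only score-dependent route they describe, interruption of access on worsening, is worded alike for both app arms, which is closest to the row with little bias. The direction is not fixed either: informative loss in the active arm alone overstates the benefit.

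A reader might also infer that dropout becomes missing at random once weekly scores are included. That is too strong. Disengagement from the app also ends score collection, and the monitoring section itself expects some weekly forms not to be completed. The weekly scores make the assumption more plausible but do not secure it.

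It could be said that auxiliary use of these scores belongs in an analysis plan that is not shown. It may, but the article states the primary model's visit set outright, and that statement is what the point addresses. The objection that weekly scores achieve nothing while carry-forward remains is correct, and the fix takes it in.

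**Conclusion.** The point holds as a worthwhile improvement to a stated analysis choice. It does not show that the trial's result would be wrong. The primary model leaves out scores on its own outcome scale, and for participants last seen at weeks 1, 2, 4 or 5 these include the latest one.

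The main gain is protection against bias: little is needed if dropout acts alike in both app arms, about 0.03 to 0.08 SD in either direction is avoided if one arm's dropout follows the score, and more only in the adverse opposite-direction case. For scale, the standard error of the contrast is about 0.19 SD. The precision gain is a few per cent. These sizes depend on the assumed covariances, dropout mechanisms and 0.40 SD effect, none of which the protocol gives.

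**What to change.** In Statistical methods, for the active-versus-placebo contrast:

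- Fit a likelihood-based mixed model with categorical visit to all CESD-R scores from baseline to week 6 and report the week-6 contrast. Alternatively, use the weekly scores as auxiliary variables in multiple imputation.
- Remove the first-value carry-forward rule from this analysis.
- Let wait-list participants contribute the visits they have.
- Keep the 3-month follow-up in the model or state a separate analysis for it.
- Retain the four-assessment fit as a sensitivity analysis.

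The monitoring section's wording, which covers every participant, should also be reconciled with the wait-list schedule under Participant timeline.

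The cost is wording and some modelling, with no new data. An unstructured covariance over seven visits has 7×8/2 = 28 parameters, against 3×4/2 = 6 for baseline, week 3 and week 6. The wait-list arm lacks four of the seven visits by design, and some weekly scores will be missing intermittently.

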## Discussion

This study describes a randomized clinical trial testing a smartphone app aimed at reducing moderate depressive symptoms. The target of this trial represents people with moderate depressive symptomatology. As there is no current clear evidence about the efficacy of smartphone apps in reducing depressive symptomatology, despite some preliminary studies that have shown promising results [19–24], this research can contribute substantially to clarifying the therapeutic merits of mobile interventions.

This study’s main aim is to test a newly developed app based on the CBT theory of depression to determine primarily whether this app is clinically useful in decreasing moderate depressive symptoms when compared with an active placebo. To our knowledge, this is the first attempt to test the efficacy of a smartphone app for depressive symptomatology in the form of an RCT that includes an active placebo condition. As such, this can substantially add to the body of evidence supporting the use of apps designed to decrease depression.

Additionally, this study investigates the app’s potential to contribute to the reduction of general negative affect, increasing positive affect, boosting satisfaction with life, and modifying depressogenic cognitions.

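### The primary analysis is an undifferentiated three-group comparison that does not carry over the app-versus-placebo aim, and the stated multiplicity rule covers only secondary and other outcomes

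*Protocol article*

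**What the plan says.** Protocol article, Statistical methods, plans a mixed-effects regression over the assessments and defines the main analysis in one sentence: "The main analysis will compare groups (active intervention, PI, and WL) in terms of the level of depressive symptoms". It does not say whether this is one omnibus test or several pairwise tests, or which contrast decides the trial. The next sentence gives the only multiplicity rule in the document: "When the analysis of secondary/other outcomes is performed, the error probability will be adjusted according to the number of group comparisons performed".

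The aim is narrower. The Discussion says the study is meant "to determine primarily whether this app is clinically useful in decreasing moderate depressive symptoms when compared with an active placebo". The background paragraph of the Abstract and the Objectives section say the same, and Objectives explains that the sham comparison is what separates a genuine effect from a placebo effect.

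The Sample size section uses an ANOVA ("repeated measures, between factors"), "assuming an alpha level of 0.05, a statistical power of 0.80, and a small to medium effect size", with f = 0.2. The result is 165 participants. This sizes a test across all three groups, not the app-versus-placebo contrast.

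**The concern.** The authors recognised that three arms create several group comparisons, but wrote the correction only for outcomes that do not carry the confirmatory claim. The sentence defining the primary analysis treats the three arms alike, so nothing in it prevents a difference from the wait-list being counted as primary success.

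The trial exists because, as Framework and rationale argues, a digital placebo effect may explain earlier positive app results. A primary result driven by the wait-list cannot separate the app from that effect. The headline claim could then rest on a contrast that does not answer the question, possibly at an error rate above the nominal 5%.

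**Working it through.** **Inputs from the document.** Three arms with a one-in-three chance of placebo (Trial design); alpha 0.05, power 0.80, f = 0.2 and N = 165, that is 55 per arm (Sample size); recruitment target 220, about 73 per arm.

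**Assumed, because not stated.** Pairwise tests are two-sided. The number of measurements m and their correlation ρ are varied below.

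**Step 1: reproduce the plan's figure.** For a between-groups factor with repeated measures, the noncentrality is λ = f² × N × m / (1 + (m − 1)ρ), with (2, N − 3) degrees of freedom.
- With m = 3 and ρ = 0.5, λ = 0.04 × 165 × 3 / 2 = 9.9.
- The smallest N reaching 80% power is 164, which is 165 with equal arms. Power at 165 is 0.804. The stated 165 is reproduced.

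**Step 2: chance of at least one false positive when all three arms are equal.** Simulation with 1,000,000 replicates and a pooled-variance t test, run at 55 and at 73 per arm.

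| Reading of the main analysis | Error rate |
|---|---|
| App versus placebo as sole primary test | 5.0% |
| One omnibus test, or pairwise tests only after it is significant | 5.0% |
| Two ungated contrasts, app versus placebo and app versus wait-list | 9.0% |
| Three ungated pairwise tests, any one counting | 12.2% |

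Treating the tests as independent would give 1 − 0.95² = 9.75% and 1 − 0.95³ = 14.3%. The simulated figures are lower because the contrasts share arms.

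**Step 3: what an omnibus test shows when the app adds nothing over placebo.** Put the app and placebo means at 0 and the wait-list mean d standard deviations worse.
- The grand mean is d/3.
- The variance of the three means is [2(d/3)² + (2d/3)²] / 3 = 2d²/9, so f = d√2/3.
- Setting f = 0.2 gives d = 0.6/√2 = 0.42.

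Omnibus power depends on f and not on which arm differs. The power of 0.804 from Step 1 therefore applies: the test is significant about 80% of the time with no app-versus-placebo difference. At ρ = 0.5 the figure is 0.75 for m = 2 and 0.83 for m = 4. Over m = 2 to 4 and ρ = 0.3 to 0.8 it runs from 0.67 to 0.92.

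**Step 4: does gating protect the app-versus-placebo contrast itself?** Yes. With app equal to placebo and the wait-list different by 0.3 to 3 SD, the gated false-positive rate for app versus placebo was 4.1% to 5.0% at 55 per arm and 4.4% to 5.0% at 73. The exposure lies in which result is called primary, not in that contrast's own test.

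**Step 5: what naming one contrast saves compared with adjusting all three.** For an illustrative app-versus-placebo difference of 0.4 SD, with 55 per arm, m = 3 and ρ = 0.5, the SD of a participant's mean is √((1 + 2 × 0.5)/3) = 0.816. The standardised difference is 0.4 / (0.816 × √(2/55)) = 2.57. Normal-approximation power is 0.73 at alpha 0.05 and 0.57 at 0.05/3 = 0.0167.

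**The case against.** The strongest reply has four parts.

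- **The lead comparison is named.** The Abstract, Objectives and Discussion all give it. A reader of Statistical methods alone might infer that the trial has no lead contrast, and that would be wrong. What is missing is the link from the aim to the primary analysis.
- **Twelve percent does not follow from the text.** A reader might infer that the plan carries that false-positive risk. It arises only if all three pairwise tests are run, without an omnibus gate, and any one counts as success, including placebo against wait-list. The document states none of these, and the ANOVA sizing fits a single 5% test. For app versus placebo alone the error rate does not exceed 5% under any of these readings. Nor do the documents support multiplying the count by visits, since the plan is one mixed model over time and not separate tests at each visit.
- **The rule is silent on the primary outcome.** The quoted sentence does not say that primary comparisons will go unadjusted, and contrast order may sit in an analysis plan that is not shown.
- **An omnibus test controls error.**

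The first two parts stand and limit the size of the point. The third stands only in part: the article does not merely leave multiplicity to another document. It states a rule, limits it to non-primary outcomes, and defines a main analysis that does not match its stated aim. The fourth is true only when all three arms are equal. Step 3 shows that a significant omnibus test is the expected result in the very scenario the trial was built to exclude.

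**Conclusion.** The point holds as a mismatch between aim and primary analysis, combined with a multiplicity rule confined to secondary and other outcomes. The false-positive risk when all arms are equal is a range: 5% under the omnibus, gated or single-contrast readings, 9% for two contrasts against the app, and about 12% as the upper case.

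The more serious consequence does not depend on inflated error. A correctly sized omnibus test would be positive about 80% of the time when only the wait-list differs, by about 0.42 SD. That figure belongs to the ANOVA used for sizing, with 3 measurements, correlation 0.5 and N = 165. The planned mixed model may give a different value, but a test across all three groups still cannot by itself show that the app beats placebo.

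**What to change.** In Statistical methods, state that the single primary test is the app-versus-active-placebo contrast on the CESD-R, taken from the planned mixed model, at two-sided 0.05. State that the wait-list contrasts on the CESD-R are tested afterwards, either in fixed sequence or under the adjustment already promised for secondary outcomes. Error control does not require replacing the trajectory model with a single time point; that is a separate choice.

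The cost is two sentences and no change in the sample-size target. The named contrast keeps the full 0.05, which for a 0.4 SD difference means power of 0.73 instead of the 0.57 left by a three-way Bonferroni split (Step 5 assumptions). The small downside is that the wait-list contrasts lose unadjusted primary status, and in a fixed sequence they are formally tested only if app versus placebo succeeds. The change does not show that 165 is enough for the named contrast, because the protocol sized a three-group test.
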